### Step 2: Specify the Target Behavior

The goal of step 2 was to define the target behavior to be specific and measurable [19]. Mean knowledge, health belief, risk perception, and avoidance behavior scores from a previous study by Trifunovski et al [16] were used to calculate the appropriate group mean difference between the control and intervention groups. Using a Likert scale, participants’ knowledge and awareness, health beliefs, risk perceptions, and avoidance behaviors were evaluated through a composite score for each construct. For example, lower scores indicated lower knowledge and awareness. In this study, women scored an average of 21 (SD 6) points in the avoidance behavior section (scale from 6 to 30 in the original study). This step also included reviewing the current literature on educational toolkits to ensure that our toolkit was developed using best practices to elicit behavior change. Our research team conducted a comprehensive scoping review to answer the following research question: “What elements of educational toolkits contribute to improved risk perception and positive behavior change concerning the reduction of toxicant exposure from PCPs?” [21]. For this scoping review, we searched both academic studies and nonacademic literature, such as reviews of mobile apps that focus on PCPs, to ensure that we were able to analyze the literature surrounding educational toolkits that focus on increasing risk perception and promoting behavior change regarding harmful PCPs [21]. After the completion of this scoping review, and to further understand the aspects needed in an environmental health literacy toolkit, we also conducted a comprehensive systematic review to examine the current literature on environmental health literacy toolkits [22]. For this systematic review, we had two primary objectives:

To identify the characteristics of existing environmental health educational toolkits related to environmental health and behavior changeTo identify the methods and data collection tools used to evaluate the effectiveness of these educational toolkits

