### Step 2: Specify the Target Behavior

This was promoting women’s paraben-free behaviors by increasing women’s knowledge and access to information, health beliefs, and risk perceptions using an educational toolkit that has been informed by the literature. Our hypothesis was that women who had access to the Paraben-Free & Me educational toolkit would exhibit a 10% improvement in paraben-free behavior (3.5 points), knowledge and access to information (3.5 points), health beliefs (2.5 points), and risk perception (2.5 points) in group mean difference scores when compared with those who did not have access to the toolkit.

Our scoping review of academic sources and users’ mobile app reviews revealed four themes of elements commonly observed in environmental health educational toolkits for facilitating behavior change: (1) toolkit accessibility and affordability, (2) simplicity of the presented information, (3) personalization of features, and (4) a clear focus on knowledge sharing [21]. This review highlighted not only the elements that are currently being featured in existing toolkits but also elements that users wish were included based on their reviews. Our systematic review highlighted the importance of toolkits being interactive, accessible, and personalized [22]. These factors were integrated into the development of our toolkit to ensure behavior change.

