### Future Directions and Implications

Following the IDEAS framework, the next step for this project will be assessing the effectiveness of the Paraben-Free & Me toolkit using a randomized controlled approach. This includes piloting the toolkit for potential efficacy and usability (step 8), evaluating the efficacy through a randomized controlled trial (step 9), and sharing the intervention and findings (step 10). A single-site study at Ontario Tech University will be conducted to measure the effectiveness of the toolkit among female students between the ages of 18 and 35 years, with half of the participants in the control group and half in the intervention group. The primary outcome of assessment will be paraben-free behavior, and secondary outcomes will include knowledge and access to information, health beliefs, and risk perceptions. Both groups will complete the questionnaire that assesses these outcomes at baseline and after the intervention period. Group mean differences and 95% CIs will be analyzed to determine whether there were differences between baseline and follow-up scores. Future iterations of the toolkit may include developing simple games, replacing weekly quizzes with daily morning quotes, and potentially adding incentives through gift vouchers or promotional codes for paraben-free products.

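### The only analysis sentence is worded as a baseline-versus-follow-up comparison, while the hypothesis is toolkit versus no toolkit; the between-arm contrast should be named

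*Protocol article*

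**What the plan says.** The trial is sketched in one paragraph of the Protocol article, under Future Directions and Implications. Participants are split "with half of the participants in the control group and half in the intervention group". On outcomes it says "The primary outcome of assessment will be paraben-free behavior", with knowledge and access to information, health beliefs and risk perceptions as secondary. On timing: "Both groups will complete the questionnaire that assesses these outcomes at baseline and after the intervention period". One sentence covers the analysis: "Group mean differences and 95% CIs will be analyzed to determine whether there were differences between baseline and follow-up scores".

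The hypothesis is in Results, Step 2. Women with the toolkit "would exhibit a 10% improvement in paraben-free behavior (3.5 points"), and this is expressed "in group mean difference scores when compared with those who did not have access to the toolkit". Methods, Step 2 uses the same term when it says that scores from a previous study "were used to calculate the appropriate group mean difference between the control and intervention groups".

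**The concern.** The hypothesis asks whether women given the toolkit do better than women not given it. The analysis sentence says its purpose is to find out whether scores differ between baseline and follow-up. These are different questions, and only the first uses the randomization.

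The difference matters here because both arms complete the same paraben questionnaire twice. Answering it at baseline may itself prompt women to read labels or look up parabens, and outside publicity would reach both arms. Either would raise follow-up scores without any contribution from the toolkit. A pre-post change in the toolkit arm includes such shifts; an intervention-minus-control difference removes whatever is common to both arms. If the sentence were applied literally, a trial of an ineffective toolkit could report a confidence interval above zero on its primary outcome and describe that as the planned result.

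**Working it through.** **Step 1: the three places side by side**

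| Place | Term used | Contrast described |
|---|---|---|
| Methods, Step 2 | group mean difference | control versus intervention |
| Results, Step 2 (hypothesis) | group mean difference scores | access versus no access to the toolkit |
| Future Directions and Implications (analysis) | group mean differences, 95% CIs | baseline versus follow-up |

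The first two rows agree with each other. The third keeps the term but attaches a different comparison, and nothing else in that paragraph says that follow-up or change scores will be compared between arms.

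**Step 2: what the literal reading would cost (illustration only)**

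The article gives no sample size, power or alpha for the trial, so there is no figure of its own to reproduce.

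Inputs:
- SD 6, from Methods, Step 2: "women scored an average of 21 (SD 6) points in the avoidance behavior section (scale from 6 to 30 in the original study"). It is assumed that this SD carries over to the trial's scale and applies at both time points.
- Assumed: baseline/follow-up correlation ρ = 0.5; n = 50 per arm; two-sided 95% CI; true toolkit effect 0; both arms drift up by the same amount d.

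SD of change = 6 × √(2(1 − ρ)) = 6 × √1 = 6.

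SE of one arm's mean change = 6/√50 = 0.849.

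The probability that the toolkit arm's paired-t CI lies wholly above 0 comes from the noncentral t distribution with 49 degrees of freedom, noncentrality d/0.849 and critical value 2.01:

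| Common drift d | Noncentrality | P(toolkit arm's pre-post CI above 0) | P(toolkit arm significant, control not) |
|---|---|---|---|
| 0 | 0 | 2.5% | 2% |
| 1.0 | 1.18 | 21% | 17% |
| 1.5 | 1.77 | 41% | 24% |
| 2.0 | 2.36 | 64% | 23% |

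The last column is p × (1 − probability that the control arm's CI excludes 0), because the arms are independent and drift equally. For example, 0.41 × 0.59 = 0.24 and 0.64 × 0.36 = 0.23.

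**Step 3: the between-arm test under the same conditions**

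The expected difference in change is d − d = 0 whatever d is, so a two-sided 95% CI favours the toolkit in 2.5% of trials.

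**Step 4: sensitivity**

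Over n = 25, 50 and 100 per arm, ρ = 0.3, 0.5 and 0.7, and d = 1, 1.5, 2 and 3 points, the within-arm probability runs from 10% (n = 25, ρ = 0.3, d = 1) to nearly 100% (n = 100, ρ = 0.7, d = 3). With no drift it is 2.5%. The size of the problem is therefore set mainly by the assumed drift. The mismatch in Step 1 needs no assumption.

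**The case against.** The best defence is that the article's own vocabulary resolves the ambiguity. Both Step 2 sections use group mean difference for intervention versus control. With two randomized groups measured twice, the analysis sentence can be read as a between-arm difference, with CI, in baseline-to-follow-up change. That analysis would answer the hypothesis. The article mainly describes how the toolkit was developed, the trial takes up one forward-looking paragraph, and the full protocol and analysis plan are not shown. The error rates above also depend on a drift, sample size and correlation that the article does not give.

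Much of this stands. A reader might infer that the trial will definitely run only within-arm tests, that its planned result cannot answer its question, or that effectiveness will be judged by one arm being significant and the other not. The article does not support any of these: it mentions no per-arm interval, paired test or comparison of significance, and its earlier use of the term points the other way.

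Two things remain. First, the sentence's purpose clause names baseline and follow-up as the things compared and names no arm contrast, so the favourable reading has to be brought in from other sections. Second, leaving detail to another document explains an omission, but not a stated purpose that differs from the hypothesis.

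**Conclusion.** The point holds as a conflict in wording over the primary contrast. The analysis sentence describes a pre-post comparison, the hypothesis is between arms, and the intended between-arm analysis, though plausible, is not stated. As published, the sentence would let either analysis be reported as planned.

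The figures of about 41% to 64% against 2.5% apply only under the literal within-arm reading and the assumptions in the working (SD 6 carried over from the previous study's 6-to-30 scale, correlation 0.5, 50 per arm, common drift of 1.5 to 2 points). They show why the contrast has to be fixed in advance; they are not a forecast for this trial.

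**What to change.** Replace the analysis sentence with wording such as: *The primary analysis will estimate the intervention-minus-control difference in mean paraben-free behavior score at follow-up, adjusted for the baseline score, with its 95% CI. The same contrast will be used for each secondary outcome. Within-arm changes from baseline will be reported descriptively and will not be used to conclude effectiveness.*

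A between-arm comparison of change scores would also resolve the conflict. Baseline adjustment is preferable because it uses the same data more efficiently: at correlation 0.5 the residual SD is 6 × √(1 − 0.25) = 5.2, against a change-score SD of 6.

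The cost is one sentence. Baseline and follow-up scores are already to be collected in both arms, so no new data or participants are needed. If the sponsor already intends a between-arm analysis, the edit only confirms it.

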### Limitations

Despite the strengths of the project, there are several weaknesses as well. First, we only had 3 users, all of whom were highly educated, provide feedback on our prototype. If we had had a larger amount of feedback from a more diverse group of women (such as women who are immigrants or not proficient in using technology), our toolkit might have improved as we would have been able to incorporate feedback from a broader range of target users. Finally, pilot testing was not completed for usability and satisfaction. Conducting a small-scale evaluation of the potential efficacy and user satisfaction would have assisted in further refining the toolkit.

### Conclusions

This manuscript described the use of the IDEAS framework to guide the development of the Paraben-Free & Me toolkit, an educational resource aimed at increasing women’s knowledge and paraben-free behaviors. A scoping and systematic review was used to ensure that the appropriate characteristics were included, with feedback from the research team used to further support these findings and ensure their proper use within the development of the toolkit. The IDEAS framework provided a method for focusing on a human-centered and iterative development process to ensure that the toolkit was evidence-based and its efficacy could be evaluated. The Paraben-Free & Me toolkit has the potential to help overcome barriers faced by women from diverse backgrounds as it clearly presents evidence on the harms associated with parabens and provides practical guidance for identifying them in PCPs. By minimizing paraben exposure, the toolkit promotes better health outcomes and improved quality of life.
